## Abstract

**Background:** Workplace bullying is an important and prevalent risk factors for health impairment, reduced workability and lowered efficiency among both targets and observers. Development and tests of effective organizational intervention strategies are therefore highly important. The present study describes the background, design, and protocol of a cluster randomized controlled trial evaluating the effectiveness of an organization-wide intervention on preventing workplace bullying with a focus on promoting active and constructive bystander behavior. The main overarching goal is to develop an easy to use and standardized organizational intervention based on theory and research in the role of bystanders in bullying situations with the potential of reducing the prevalence of workplace bullying. The theoretical framework of the study is theory of planned behavior (TPB; Ajzen, 1991).

**Methods/Design:** Using a full randomized control trial (RCT) design, this project will empirically test the outcomes of an intervention program targeting bullying and harassment as the main distal outcomes and perceived behavioral control and helping behavior among bystanders as the main proximal outcome. A 1-year cluster randomized controlled design will be utilized, in which controls will also receive the intervention. About 1,500 workers from two different locations of a Norwegian industrial company will be randomized into one intervention group and two control groups with at least 400 workers in each group. A survey will be conducted electronically. With a total of three assessments over 10–12 months, the time interval between the measurement times will be 4 months. Thus, the data collection will take place at baseline, completion of the intervention and at 4 months follow-up.

**Discussion:** This study primarily aims to develop, implement, and evaluate an intervention based on the abovementioned features with the ultimate aim of reducing the prevalence of workplace bullying, by awareness raising and training of bystanders. Manager involvement and involvement of the union representative and the elected health and safety representatives is an important feature of the program. Results of the intervention study will provide important information regarding the effectiveness of preventive interventions against workplace bullying when focusing on bystanders, particularly so regarding the role of bystander awareness, bystander self-efficacy, and bystander behavioral control on the one hand and the prevalence of bullying and harassment on the other.

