1.Those who have received the intervention will have a change in **outcome variables (behavior)** from T1 to T2 as compared to those in the control group:1.1.Those who receive the intervention will have an increase in *observed workplace bullying* from T1 to T2 as compared to those in the control group due to an increased awareness.1.2.Those who receive the intervention should report lower exposure to bullying behaviors, as compared to those in the control group.1.3.Those who receive the intervention will be more likely to *intervene when observing workplace bullying* from T1 to T2 as compared to those in the control group.2.Those who receive the intervention will have a change in **independent variables (attitudes, norms, perceived control, and social climate)** from T1 to T2 as compared to those in the control group:2.1.Those who receive the intervention will have an increase *in their attitudes toward intervene constructive when observing workplace bullying* from T1 to T2 as compared to those in the control group.2.2.Those who receive the intervention will have an increase in *perceived bystander norms* from T1 to T2 as compared to those in the control group.2.3.Those who receive the intervention will have a more positive view of the *social climate* in the working group from T1 to T2 as compared to those in the control group.2.4.Those who receive the intervention will have an increase in perceived *informal surveillance* from T1 to T2 as compared to those in the control group indicating an increase in social anti-bullying norms in the working environment.2.5.Those who receive the intervention will have an increase in *perceived bystander behavior control* from T1 to T2 as compared to those in the control group.3.From T2 to T3 the control group, which will receive the intervention after T2, will show the same results of the abovementioned hypothesis as the intervention group did from T1 to T2.

An overview of the relationships studied in this intervention is given in Figure 1.

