### Study Design

This project has an RCT design that includes a range of departments from the case company, a Norwegian industry company. The company has two main locations, one on the west coast (location A) being the larger plant with some 1,600 employees and one in mid Norway (location B) being the smaller plant with some 800 employees. In location A, being the larger facility, all departments in the production part and two administrative departments will be randomly assigned to an intervention group and a control group. The control group will receive the intervention 6 months later, as will location B. As such, the location that is given the intervention last (location B) will also serve as an additional control group for the first interventions carried out in location A. Hence, we have two control groups for the initial intervention. In order to carry out a valid and reliable study of causal relationships and mechanisms, it is necessary to use a design where the study variables are measured repeatedly over time. In this project, we will use a mixed method design by combining a longitudinal survey, qualitative interviews, with this RCT design. All employees in the selected departments in the two locations of the case company will be invited to participate in a prospective questionnaire survey that will be distributed three times during a 12-month period. The questionnaire will be identical at all assessment points. It will be possible to distinguish between managers with personnel responsibility, managers without personnel responsibility, safety representatives, labor union representatives, other level employees, and the unit to which they belong. Data will be collected through *Surveyexact*, a web-based system for secure administration of questionnaires. The system is developed for the purpose of tracking individuals over time in a way that satisfies demands for anonymity and personal security and data protection. When accessing the web-based questionnaire by a link, the respondents will be asked to provide their informed consent before responding to the questionnaire. No personally identifiable information about respondents will be available to researchers, as data will be de-identified prior to analyses.

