### Assessment of Potential Bias

#### Response Bias

Due to their personal experiences, employees may be more inclined to participate in the survey and intervention if they have been exposed to or observed harassment and bullying at the workplace. This situation is likely to inflate the prevalence estimates found in our sample in case of substantial non-response among non-exposed workers. We attempt to mitigate this problem by informing the respondents of their value to the study even though they have not experienced or witnessed bullying. To motivate all organizational members to participate, information about the utility of the intervention “Grip inn/Intervene” as a tool for each work unit to assess and improve working conditions will be carefully disseminated to all key personnel. This will be ensured by holding information meetings with all managers, foremen, labor union representatives, and health and safety representatives, during which there will be an emphasis on their roles as motivators for their colleagues. Furthermore, this information will also be communicated through the case company’s intranet. To reinforce commitment in the organization, the head executive vice-president will send out information and encouragement to participate in the survey and intervention, prior to the distribution of the survey. Moreover, up to four reminders will be sent during the survey collection period. These reminders will be sent by both the researchers and managers^3^. The strict procedures for confidential treatment of data will also be highlighted.

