#### Contamination of Control Group

As the main location for the intervention study will be divided into intervention groups and control groups, there is a risk that the project may also have effects in the control groups. This is particularly the case as we may need to work quite a bit with the whole organization to secure a high participation rate in the organization. To counteract this problem, we will use location B as a second control group. Apart from a managerial level, there is little interaction between employees in the two locations of this organization.

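### The abstract presents location B as a randomised control group, but only location A departments are randomised, so the contrast with location B cannot be separated from site

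*Protocol article*

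**What the plan says.** The abstract (Methods/Design) states that about 1,500 workers from both locations "will be randomized into one intervention group and two control groups with at least 400 workers in each group". On that wording all three groups arise by randomisation.

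The Study Design section describes something else. In location A, "all departments in the production part and two administrative departments will be randomly assigned to an intervention group and a control group". Location B enters by a different route: "the location that is given the intervention last (location B) will also serve as an additional control group" for the first round of delivery in location A. The section then concludes: "Hence, we have two control groups for the initial intervention". Location B is the smaller plant, with some 800 employees against some 1,600, and lies in another part of the country.

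The section on contamination recognises that work in location A may spill over to the control departments there. Its answer is "To counteract this problem, we will use location B as a second control group", supported by the limited contact between employees of the two plants.

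The hypotheses compare with a single control group, nearly all in terms of change from T1 to T2. Under hypothesis 3 the control group receives the intervention after T2, which fits both the location A control and location B.

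**The concern.** The abstract claims a property for location B that the design does not give it. The article presents the study as a full RCT and its RCT design as new to the field, so readers will carry that claim over to any result that uses location B.

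This goes beyond wording because location B is held out as the safeguard if the randomised contrast is contaminated. The non-randomised comparison would thus be leaned on exactly when the randomised one is in doubt. Neither the contamination section nor the limitations mention that the two plants may differ for reasons unrelated to the intervention. The contamination section argues that the plants are separate, and separation does not make them comparable.

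**Working it through.** **1. What is randomised.** The two descriptions side by side:

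| | Abstract | Study Design |
|---|---|---|
| Who | "About 1,500 workers from two different locations of a Norwegian industrial company will be randomized" | Departments in location A |
| Into what | One intervention and two control groups | One intervention and one control group |
| Location B | Part of the randomised pool | Whole site, control because treated later |

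No section says that location B, its departments or the order of the two sites was drawn at random. The abstract and the Study Design section cannot both be right.

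**2. What each contrast identifies in the first phase.** Write the expected T1 to T2 change as a common part, plus a site part, plus the intervention effect where it applies, plus spill-over where it applies.

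- A intervention minus A control = effect − spill-over. The site part cancels.
- A intervention minus B = effect + (site part of A − site part of B).
- A control minus B = spill-over + (site part of A − site part of B).

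Location B has no intervention members in this phase, so a site term in the model is the same column as the group term and cannot separate the two. Working with change removes a stable difference in level. It leaves any difference in trend and any event at one plant. The first two contrasts differ by spill-over plus the site difference, and so does the third, so neither comparison can tell contamination from site.

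**3. The planned figure.** Inputs from Statistical Power: effect size 0.279, alpha 0.05, power 0.80, 204 per group. A two-sided normal approximation gives 202 per group. The t-test gives 202.6, so 203, and power at 204 is 0.803. The figure reproduces.

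**4. Illustration of the site problem.** Assumptions: no intervention effect, a site difference d (in SD) in the analysed change, m respondents per group, clustering ignored. The article gives no value for d. With c = d / √(2/m), the rejection probability is Φ(c − 1.96) + Φ(−c − 1.96).

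| m per group | √(2/m) | d = 0.05 | d = 0.10 | d = 0.20 |
|---|---|---|---|---|
| 204 | 0.0990 | 0.080 | 0.173 | 0.524 |
| 400 | 0.0707 | 0.109 | 0.293 | 0.807 |

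More respondents make it worse, because the bias stays while the standard error shrinks. If two equal-sized controls were pooled, half of d would remain, with standard error √(1/m + 1/(2m)). At m = 204 this rejects with probability 0.090 for d = 0.10 and 0.215 for d = 0.20.

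**5. What the within-A contrast costs.** Inputs: at least 400 workers per group (abstract) and 55–70% response per wave (Statistical Power). If responses at T1 and T2 are independent, completers per group are 400 × 0.55² = 121 to 400 × 0.70² = 196. Power at d = 0.279 is then 0.58 to 0.79 before any allowance for clustering. Independence matches the upper end of the article's own three-wave range: 1,500 × 0.70³ = 514.5, stated as 515. If instead the same people answered both times, completers would be 400 × 0.55 = 220 to 400 × 0.70 = 280. Under independence, 204 completers need 204 / 0.49 ≈ 417 to 204 / 0.3025 ≈ 675 workers per group.

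**The case against.** The strongest reply is that the error is one condensed sentence in an abstract. The Study Design section is clear about what is randomised, and neither it nor the contamination section calls location B randomised. An external control beside a randomised one is a legitimate choice, and limited contact between plants is a sensible reason for it. The order of contrasts may sit in a fuller plan that is not shown. All of this stands. It limits the point to the false statement in the abstract and to offering location B as a remedy without noting the site confounding. A fuller plan could order the contrasts but could not make the abstract's sentence true.

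Three stronger readings are tempting and should not be drawn.

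- A reader might infer that the two controls will be pooled, or that the more favourable one will be chosen. No section plans either, and Study Design counts them as two groups.
- A reader might infer from "Those who have received the intervention will have a change in", taken with the remark that "employees may be more inclined to participate in the survey and intervention if they have been exposed to or observed harassment and bullying", that analysis will follow attendance and so break the randomisation inside location A. The hypotheses use receiving at group level: the whole control group is said to receive the intervention after T2. The remark speaks only of a possible inclination, and the consequence it names is inflated prevalence. No section excludes or reassigns non-attenders.
- A reader might size the problem by how far two site means differ at one time. That is a difference in level, which an analysis of change largely removes.

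**Conclusion.** The point holds. The abstract misstates what is randomised: departments in location A are, and location B is a single non-randomised site. A intervention against location B is fully confounded with site in the first phase, and analysing change reduces this without removing it. The article therefore cannot offer location B as a remedy for contamination without saying that a site difference could produce the same pattern.

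The size of any bias is unknown. The rejection rates of 17% and 52% at 204 per group rest on assumed site differences in change of 0.10 and 0.20 SD and on ignoring clustering. They show sensitivity and are not a forecast. That the contrast is aliased with site rests on the design text alone. The randomised contrast within location A is sound in this respect and is described correctly in Study Design.

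**What to change.** - Correct the abstract: departments in location A are randomised to intervention or control, and location B is a non-randomised external control.
- Name intervention against control departments within location A, grouped by department allocation, as the confirmatory contrast.
- Report A intervention against location B separately as a supportive, baseline-adjusted, non-randomised comparison. Do not pool location B with the location A control.
- State in the contamination section that neither a disagreement between these two contrasts nor a difference between A control and location B can distinguish contamination from a site difference.

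The cost is wording and a fixed order of analyses. The real downside is that the confirmatory contrast uses fewer workers and may be diluted by contamination. At the stated minimum of 400 per group it could fall short of the planned 204 at T1 to T2 (121–196 under independent response), so the expected number of completers within location A should be stated with it.

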## Introduction

Workplace bullying and harassment is a prevalent problem in contemporary workplaces all around the globe (van de Vliert and Einarsen, 2014; Zapf et al., 2020), with documented devastating effects on the targets health and well-being (Niedhammer et al., 2012; Lesuffleur et al., 2014; Nielsen and Einarsen 2018; Jacobsen et al., 2020; Mikkelsen et al., 2020). The concept of workplace bullying and harassment refers to a systematic form of aggression and social exclusion where an employee, persistently and over a period of time, is exposed to negative actions from superiors or coworkers where the employee finds it difficult to defend himself/herself against the aggression (Olweus, 1993; Einarsen et al., 2020). Synthesized findings from systematic reviews and meta-analyses of cross-sectional and longitudinal studies show that targets of such treatment have an elevated risk of mental and somatic health problems (Nielsen and Einarsen, 2012; Nielsen et al., 2014; Verkuil et al., 2015), including symptoms of posttraumatic stress (Nielsen et al., 2015) and long term sickness absence (Nielsen et al., 2016). While individual targets even risk exclusion from working life (Glambek et al., 2016), organizations risk productivity loss, loss of reputation, and even financial losses (Hassard et al., 2017; Hoel et al., 2020).

With an estimated global prevalence rate of up to 15% of more severe cases (Nielsen et al., 2010), the development of effective preventive efforts is paramount. However, to this date, few interventions have been tested empirically and few have been conducted with high quality research designs. Furthermore, those interventions that have been properly examined in research have mainly been beneficial with regard to reducing aggressive behavior of low intensity, such as incivility, whereas they have been unsuccessful and ineffective with respect to more severe cases of workplace bullying (Hodgins et al., 2014; Escartin, 2016; Gillen et al., 2017).

An explanation for why most previous attempts at interventions toward workplace harassment bullying have failed may be that the measures undertaken have been all-encompassing interventions focusing on the more broad issue, such as respect, dignity, and civility, or on psychosocial work environment factors in general, rather than explicitly addressing bullying and harassment (Probst et al., 2008; Einarsen et al., 2009; Osatuke et al., 2009). Hence, most interventions have been general rather than selective and indicative, as in the case in the present study. Hence, an intervention that aims to reduce the occurrence of workplace bullying should have a clear focus on specific wanted and unwanted conduct, in our case by directly addressing bystanders behavior when observing acts of bullying at work. Since most cases of workplace bullying escalates over time with targets being exposed to varying degrees of interpersonal aggression – from occasional exposure to negative acts of mere incivility to being severely victimized on a daily basis (Einarsen et al., 2020) – preventive interventions should address bullying in its early phases.

Another explanation for why previous interventions have failed is that organizational interventions are usually determined to be effective based on whether exposure to an intervention condition preempted a statistically significant improvement in a targeted distal outcome. However, according to Biggs and Brough (2015), several reviews have concluded that the success of organizational interventions is largely determined by facets of the context in which they are implemented (i.e., intervention context), how they are implemented, and to whom they are implemented (i.e., intervention process). When evaluating interventions, it is therefore important also to evaluate mediating proximal effects that are theoretically linked to targeted distal outcomes, that is, factors that hinder or facilitate the main outcome of the intervention (Nielsen and Abildgaard, 2013). In the case of workplace harassment and bullying, bystander behavior and bystander intervention has been proposed as a specifically important proximal variable with regard to the further development of workplace bullying (D’Cruz and Noronha, 2011; Pouwelse et al., 2018; Ng et al., 2019). Addressing the role of bystanders may therefore be beneficial when crafting an effective intervention. Specifically, by promoting social support and constructive behaviors among bystanders (mediating proximal effects), one may be able to also reduce the overall occurrence of workplace harassment and bullying in the longer run. Hence, the underlying intervention theory assumes a mediated process, whereby perceived or actual changes to distal outcomes (i.e., reduced occurrence of harassment and bullying) occur due to perceived or actual changes in proximal outcomes (bystander intervention).

A third explanation for why previous interventions toward harassment and bullying have failed is that they have not been conducted with sufficient methodological rigor to contribute to the evidence base for addressing the problem of workplace bullying and incivility (Escartin, 2016; Gillen et al., 2017). According to Gillen et al. (2017), there is presently only very low-quality evidence that organizational and individual interventions may prevent harassment and bullying in the workplace. Hence, there is a need for large well-designed controlled trials of preventive interventions employing both distal and proximal factors, preferably with a randomized control trial (RCT) design.

### Theoretical Model for the Intervention

The present study builds on the overarching proposition that having bystanders intervene more often and more constructively in everyday bullying and harassment episodes, preferably before the bullying situations have escalated, should help to reduce the occurrence and prevalence of this pertinent problem over time. The present intervention study then builds on the theory of planned behavior (TPB; Ajzen, 1991) to achieve this. The TPB proposes three determinants of a person’s intentions, behavior, and any following behavioral changes, attitude, subjective norms, and perceived behavioral control. These three factors will be seen as proximal and mediating outcomes, while observed and perceived exposure to bullying, including observed social climate, will be the more distal and final focal outcome. In our context, attitude will be addressed by the very nature of the intervention, that is, creating awareness and changes in attitudes regarding the existence and nature of workplace bullying and one’s own attitudes and perceived typical bystander behavior in such situations. The intervention is further designed to alter participants’ subjective norms by increasing the perceived social pressure to perform constructive bystander behavior in such situations. Lastly, by showing when and how bystanders may intervene constructively (Ajzen and Madden, 1986; Ajzen, 1991), the intervention should alter individuals’ perceived behavioral control in specific situations, the latter implying the extent to which the behavior is perceived to be under volitional control. Thus, developing a psychosocial climate in the organization where individual attitudes and social norms foster constructive bystander behavior, while also enhancing the employees’ perceived behavior control as bystanders, is hypothesized to be crucial in combating workplace bullying in organizations.

Accordingly, in addition to investigate any changes in bullying and harassment in the working environment, the present study will examine whether attitudes, social norms, and perceived behavioral control of those who have received an intervention called “Intervene,” will be changed and possibly influence bystander behavior in bullying situations. Ultimately, the intervention should reduce the occurrence of bullying and harassment and improve the social climate at work. As such, we hypothesize the following regarding these proximal outcomes:

1.Those who have received the intervention will have a change in **outcome variables (behavior)** from T1 to T2 as compared to those in the control group:1.1.Those who receive the intervention will have an increase in *observed workplace bullying* from T1 to T2 as compared to those in the control group due to an increased awareness.1.2.Those who receive the intervention should report lower exposure to bullying behaviors, as compared to those in the control group.1.3.Those who receive the intervention will be more likely to *intervene when observing workplace bullying* from T1 to T2 as compared to those in the control group.2.Those who receive the intervention will have a change in **independent variables (attitudes, norms, perceived control, and social climate)** from T1 to T2 as compared to those in the control group:2.1.Those who receive the intervention will have an increase *in their attitudes toward intervene constructive when observing workplace bullying* from T1 to T2 as compared to those in the control group.2.2.Those who receive the intervention will have an increase in *perceived bystander norms* from T1 to T2 as compared to those in the control group.2.3.Those who receive the intervention will have a more positive view of the *social climate* in the working group from T1 to T2 as compared to those in the control group.2.4.Those who receive the intervention will have an increase in perceived *informal surveillance* from T1 to T2 as compared to those in the control group indicating an increase in social anti-bullying norms in the working environment.2.5.Those who receive the intervention will have an increase in *perceived bystander behavior control* from T1 to T2 as compared to those in the control group.3.From T2 to T3 the control group, which will receive the intervention after T2, will show the same results of the abovementioned hypothesis as the intervention group did from T1 to T2.

An overview of the relationships studied in this intervention is given in Figure 1.

